### Procedures

#### VR Program Development 

The VR-ACT intervention content will adapt ACT-based interventions for chronic pain that were previously developed and tested by the research team (eg, the face-to-face COMP.ACT program [33] and the online iACTwithPain platform [34]) into a VR format and tailored to CPSP. The research team will adapt experiential practices (eg, mindfulness meditation) and exercises (eg, values clarification and commitment to valued action) into a VR format through VR headset equipment (MetaQuest). The VR-ACT content will be developed through an “Unreal Engine” application with multiple rooms and different designs/environments, allowing the user-patient/participant to explore those that best suit their current need (eg, pain alleviation; emotional regulation training; establishing valued-based goals for the day) and/or the exercise suggested by the VR system (each module will have a suggested sequence; see Textbox 1).

An embedded registration system will be developed to monitor the progress and number of complete or incomplete sessions and exercises, which will be indicators of usability. This will enable the assessment of preferred time of usage and other user-centered information that can be further utilized in VR-ACT patient-centered tailoring. This registration will be supported by a centralized database and allocated to a server within the University of Coimbra, Portugal. Simultaneously, the research team will develop the content and format of the Sham VR control condition, which will be delivered through the same VR headset equipment, but with different content: 8 distraction-based exercises delivered via 2D nonimmersive video animations.

Textbox 1.The VR-ACT intervention content.
**Modules 1 and 2: Awareness Regulation Skills**
Welcome to VR-ACT: control as the problem, and not the solution (Avatar Therapist)Introduction to Mindfulness (Avatar Therapist)Mindful breathing practiceBody-scan practiceSoothing Rhythm Breathing practiceMindfulness of thoughts practice (Leaves on a Stream).
**Modules 3, 4, and 5: Acceptance of Pain and Internal Experiences**
Introduction to willingness and acceptance: Why accept? (Avatar Therapist)Letting go of control—part I: the quicksand metaphor (adapted to immersive VR)Letting go of control—part II: Joe the bum metaphor (adapted to immersive VR)Mindfulness of difficult emotions practiceAccepting with self-compassion: soften, soothe, and allow practice.
**Modules 6, 7, and 8: Behavior Change and Valued Action**
Introduction to Values (Avatar Therapist)The passengers on the bus metaphor (adapted to immersive VR)Mindfulness meditation on values: rediscovering what matters to me.Interactive game: 4 steps to committed action90th birthday imagery practice (adapted to immersive VR)Life after VR-ACT: awareness and acceptance practice as building blocks of valued action.

#### Data Collection

The research team members, who are physicians at the Neurology Service, the Pain Unit, and/or the Rehabilitation Unit of ULS-Coimbra, Portugal, will invite participants and inform them of the aims and conditions for participation. Those who provide written informed consent will be screened for medical eligibility. Then, psychological eligibility will be individually assessed, online and at a time preferred by participants, by the clinical psychologists of the research team, for severe neurocognitive and psychiatric symptoms (using Mini Mental State Examination and a semistructured clinical interview adapted from Structured Clinical Interview for DSM). Those who meet criteria for severe psychiatric disorders and/or cognitive impairment will be excluded from the study, given feedback, and advised to seek medical/psychological consultation. Eligible participants will receive the link to the online preintervention assessment (T0) self-report protocol. A task-oriented (see Section B in Multimedia Appendix 1) functional magnetic resonance imaging (fMRI) will be scheduled to collect preintervention data on the functional connectivity of the triple network (DMN, SN, and FPN). Participants will then be randomly assigned by a member of the research team to 1 of 2 conditions (EC and CC) using random permuted blocks to ensure balance in age (via an online randomizer, eg, random.org [35]). Participants will be informed of the starting date via telephone (or alternatively via email). The medical/nursing collaborators and the research team members not involved with the implementation monitoring will be blinded to the allocation. The two conditions will be masked to participants by not explicitly informing whether the content of the VR is 3D (VR-ACT) or 2D (Sham VR), with both being delivered through the same model of VR headset (MetaQuest 3.0). Nevertheless, for ethical reasons, the two conditions in the study are described in the patient information sheet. A scheduled meeting in the ULS-Coimbra will be held to provide headset devices to participants. Three groups or waves of recruitment and VR-ACT implementations will be conducted (group 1, n=10; group 2, n=10; group 3, n=10; see Figure 1). At the end of implementation, participants will return the devices and will conduct the post-intervention assessment (T1): online psychosocial self-report data collection; and functional connectivity of the triple network data collection (fMRI). Additionally, participants in the EC will be interviewed online by a research team member who is blind to the allocation to collect qualitative data on the acceptability and usability of the VR-ACT (see Section A in Multimedia Appendix 1). The time points of measurements are described in the SPIRIT figure (See Figure 2).

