### Design

** **The current project will conduct a parallel-group randomized controlled trial design and will follow a multimethod approach (qualitative and quantitative assessments) to assess the feasibility of the VR-ACT delivery [31]. The experimental condition (EC): the VR-ACT program: 8 modules of 3D immersive skills training (2 targeting awareness regulation skills; 3 promoting acceptance; 3 focused on behavioral change and commitment to valued action). To assess the preliminary efficacy and control for possible placebo effects, the control condition (CC) will consist of 8 nonimmersive 2D distracting video animations delivered through a VR headset (Sham VR). Participants in both conditions will use the VR devices throughout 8 weeks. Each module will be available weekly in both conditions and have a duration of 20 minutes. Participants in the CC will be able to use the VR-ACT after the final assessment (see Figure 1).

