#### Sample Size Calculation

 The study was powered for a large final timepoint between-group effect size (standardized mean difference=0.8), allowing for a variant autoregressive ρ over 2 measurements (preintervention and postintervention; 1 and 0.8) to accommodate the likely instability of the outcome variable(s). Setting the α at .05 and a minimum of 80% power, a minimum sample size of N=30 is required (EC: n=15; CC: n=15). We used the power.mrmm function from the R “longpower” package, through WebPower. A sample size of 15 to 30 participants is also sufficient to attain saturation in qualitative analyses conducted through interviews [32].

 To minimize dropout, (1) 2 phone calls will occur during the VR-ACT implementation to address questions on the VR-ACT content. (2) We also expect minor technical difficulties when using the VR headset. At the beginning of each module, an avatar therapist will provide a welcome message, reminding you of the research team’s contact information in case of any technical problems. Before the implementation, an online group meeting will be conducted to introduce the VR headset to participants in both conditions and help with navigation. (3) To promote engagement, weekly emails will be sent to all participants reminding them to use the VR headsets. Also, after the VR system registers 3 days of absence, automatic reminders will be sent to the participants' emails.

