### Data Analyses: Feasibility and Preliminary Efficacy

The feasibility of VR-ACT will be assessed qualitatively through open-ended questions (eg, “What would you say were the benefits of using the VR-ACT headset?,” “What have you learned from the VR-ACT program?”) designed to explore adherence, engagement, and acceptability of the intervention (see Section A in Multimedia Appendix 1). Thematic analyses will be conducted with the support of NVivo, and common themes in each question will be categorized. Also, feasibility will be quantitatively assessed through (1) dropout rate, (2) number of usage of the VR headset (embedded software usage monitoring), (3) percentage of intervention completion, (4) a 5-point Likert scale measuring usefulness, comprehensibility, and likelihood to continue using learned skills. The usability of the VR-ACT will be quantitatively assessed through the System Usability Scale.

The preliminary efficacy of VR-ACT will be pilot tested through 2 statistical methods: (1) intention to treat analyses, using linear mixed models to examine statistically significant change over time, moderated by allocation, and post hoc differences, adjusted for multiple comparisons using the Bonferroni technique; (2) reliable change index for each outcome for preintervention to postintervention timepoints, to assess clinically significant individual changes [48]. Network-based statistics [49] will be used to assess significant differences in network connectivity within and between conditions.

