## Discussion

### Expected Scientific Contribution of VR-ACT

This protocol outlines the feasibility and preliminary efficacy study of the VR-ACT project. The project adopts a multidisciplinary approach by integrating scientific knowledge from medicine, neuroscience, psychology, and computer science and engineering to develop an ACT-based VR self-management program that aims to help patients with CPSP improve their pain management skills and mental health. It employs a mixed methods approach, measuring feasibility and preliminary efficacy through both quantitative and qualitative methodologies. It is expected that (1) the implementation of VR-ACT will be feasible, measured by adherence (ie, attrition rate), engagement (number of VR usage; completion), and acceptability (qualitative postintervention assessment); (2) the VR-ACT program will be significantly more effective in reducing pain intensity and disability, and psychopathological symptoms, and in increasing quality of life, as well as in reducing functional connectivity of the triple network (fMRI), than the Sham VR.

This study is expected to have potential scientific and societal contributions: (1) development of an innovative cost-effective evidence-based pain management and mental health resource for patients with CPSP that integrates recent evidence on protective factors in CP (eg, acceptance-based emotional regulation skills, and attentional redirection) using technologies with potential personal and societal economic sustainability, thus being in alignment with the 2030 agenda for sustainable development of the United Nations (eg, access to physical and mental health and well-being for all); (2) a multimethod approach to feasibility and efficacy, by integrating qualitative and quantitative data, as well as both psychological and neuroimaging data, which will add to the literature a multilevel understanding of (preliminary) efficacy. The project will potentially open a new avenue of research in CPSP (ie, the development of self-regulatory skills through digital solutions in CPSP rehabilitation) and tentatively reinforce the need for biopsychosocial multimodal approaches to CPSP to be included in the training of health professionals working with CPSP. These expected results on the feasibility and preliminary efficacy of VR-ACT in CPSP will serve as a reference point for a future, larger, multicenter, long-term, cross-cultural study.

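### The interviewer is called blind to allocation, but only VR-ACT participants are interviewed, so every interview reveals the arm

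*Protocol article*

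**What the plan says.** Five statements in the protocol article bear on this point.

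- **Who interviews whom.** Data Collection: "participants in the EC will be interviewed online by a research team member who is blind to the allocation". The stated purpose is "to collect qualitative data on the acceptability and usability of the VR-ACT". No interview of control condition (CC) participants is described.
- **What is asked.** Data Analyses gives two example open-ended questions, and both name the experimental product. One of them is "What have you learned from the VR-ACT program".
- **Who has used VR-ACT by then.** Design: "Participants in the CC will be able to use the VR-ACT after the final assessment".
- **General blinding rule.** Data Collection: "The medical/nursing collaborators and the research team members not involved with the implementation monitoring will be blinded to the allocation".
- **Numbers.** Sample Size Calculation: "a minimum sample size of N=30 is required (EC: n=15; CC: n=15"). The same section adds: "A sample size of 15 to 30 participants is also sufficient to attain saturation in qualitative analyses conducted through interviews".

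The limitations paragraph of the Discussion accepts that participants may work out which condition they are in. It does not mention the interviewer.

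**The concern.** An interviewer who sees only one arm, and asks about that arm's intervention, knows the allocation of each person interviewed. The article nevertheless states the opposite as a feature of the design.

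Two things are at stake.

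- **The first objective.** Study Objectives defines feasibility by retention and acceptability, and the Discussion names "acceptability (qualitative postintervention assessment") as the measure behind the feasibility expectation. The interviewer belongs to the research team, which also develops the VR-ACT content. Blinding is the only safeguard the article states for the interviewer. If the claim is carried into the results paper, readers may credit the interviews with a protection they do not have.
- **Blinding elsewhere.** A team member who starts out blinded under the general rule will know who is in which arm once the interviews are done. If that person later handles fMRI or outcome data, blinding there is lost too. The article does not say who does that work.

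**Working it through.** The article gives no figure to reproduce here. The check sets the statements side by side and adds one conditional probability.

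**Inputs**
- EC n = 15, CC n = 15, total 30 (Sample Size Calculation).
- Interviewed group: EC only (Data Collection).
- CC access to VR-ACT before the final assessment: none (Design).

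**Step 1. What an interview reveals.** Under the stated rule:

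P(EC | interviewed) = EC interviewed / all interviewed = 15/15 = 1.0

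For comparison, if both arms were interviewed in full:

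P(EC | interviewed) = 15/30 = 0.5

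Only the second arrangement leaves anything for the interviewer to be blind to, and only until the answers give the content away.

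**Step 2. Whether the questions could conceal the arm.** They could not. The example questions name VR-ACT, and a control participant would have had no experience of it to report. The topic identifies the arm independently of who is invited.

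**Step 3. What the interviewer can infer about the others.** If all 15 EC participants are interviewed and the interviewer knows who is in the trial (an assumption), then 30 − 15 = 15 participants remain, and all are controls. If some EC participants are not interviewed, the inference about the rest is less than certain, but the arm of each interviewee is still known.

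**Step 4. Consistency with the general rule.** Data Collection blinds team members outside implementation monitoring. An interviewer described as blind should belong to that group. By Steps 1 and 3 the interviewer no longer fits it after interviewing, so the two statements in the same section cannot both hold for this person.

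**Step 5. Which data depend on the interviewer.**

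| Data source | Depends on the interviewer, as described? |
|---|---|
| Post-intervention interviews | Yes |
| Likert ratings of the modules | No, rated by participants |
| System Usability Scale | No, self-report |
| Device usage logs | No, recorded automatically |
| Efficacy questionnaires | No, online self-report |
| fMRI connectivity | Not through the interview; only if the same person processes the scans |

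**Step 6. Number of interviews.** The cited range for saturation is 15 to 30. EC-only interviewing gives at most 15, which equals the lower bound. The upper part of the range cannot be reached under this design.

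**The case against.** The strongest reply is that blinding has no work to do here. The interviews cover one arm and are analysed thematically, so there is no between-arm contrast for the interviewer's knowledge to distort. Social desirability would operate whether or not the interviewer was blind, and the article never says that blinding guards against it. Acceptability and usability also have other sources that do not pass through the interviewer. All of this stands, and it limits the consequence. It does not make the blinding statement true.

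A milder reading is that blind means only that the interviewer is not given the allocation list. That fails because the interviews themselves supply the list.

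The full interview guide (Multimedia Appendix 1, Section A) and the figures are not shown. The contradiction does not depend on them, since restricting the interviews to the EC is enough.

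A reader might infer more than the document supports:

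- **That the acceptability data are biased.** Exposure to bias can be shown; its presence and size cannot.
- **That too few interviews are planned.** Fifteen lies within the cited range. A shortfall needs an assumed loss: at 20%, 15 × 0.8 = 12 interviews remain. The article gives no expected dropout rate.
- **That early stoppers will be missed.** The text places the interviews at the end of implementation but does not restrict them to completers. Reasons for not completing are asked about separately under Feasibility Assessment.
- **That both arms must be interviewed.** This is a trade-off. The difference between 3D ACT modules and 2D videos would probably emerge in the answers, and control interviews could not add to saturation on the acceptability of VR-ACT.

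**Conclusion.** The interviewer-blinding claim is wrong as written. Allocation is revealed in 15 of 15 planned interviews, and controls can be identified by elimination if all 15 take place and the interviewer knows the participant list. After interviewing, this person also falls outside the article's own blinding rule.

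The consequence is limited. The interviews are exposed to interviewer and social-desirability bias that the stated blinding does not prevent, and the document gives no basis for sizing it. As described, the other feasibility measures and the self-report efficacy outcomes are untouched. Any effect on fMRI or outcome processing depends on who does that work, which is not stated.

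The point is worth correcting because it concerns the first objective and what the trial may claim in its report. It does not call the efficacy analysis into question.

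**What to change.** 1. In Data Collection, delete the statement that the interviewer is blind to allocation.
2. Specify instead an existing team member who took no part in developing or delivering VR-ACT.
3. State that this person takes no part in any fMRI or outcome processing that is meant to be blinded.
4. In Sample Size Calculation, state that at most 15 interviews, EC only, are planned, and that this is the lower end of the cited 15 to 30.

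The cost is a small constraint on who may interview and one fewer blinding claim to report. No extra participants, visits or interviews are needed.

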
**Figure 2. F2:**
[figure not shown]
SPIRIT figure of the VR-ACT study. ^a^Conducted by the medical and nursing collaborators of the research team. ^b^Conducted by a clinical psychologist member of the research team. ^c^See Section A in Multimedia Appendix 1. ^d^From 0=not at all appropriate to 4=very much appropriate. ^e^Please let us know why you decided not to complete the data collection.

#### Feasibility Assessment

##### Assessment of Data Collection and Randomization

The feasibility [36] of the recruitment and data collection will be assessed via (1) the number of participants lost from screening to randomization; (2) *appropriateness* of size, format, and content of the assessment protocol, by responding to a Likert-like scale (from 0=not at all appropriate to 4=very much appropriate) regarding (a) *accessibility* to the protocol, (b) *willingness* to provide the required information, and (c) *size* of the protocol; (3) reasons for not completing data collection (open question “Please, let us know why you decided not to complete the data collection”); (4) support provided by medical/nursing collaborators in referring potential participants measured by average number per week of participants referred by the medical/nursing team.

##### Assessment of the VR-ACT Delivery

The feasibility of the VR-ACT implementation will be evaluated in terms of (1) *adherence*: (a) percentage of participants who completed the intervention, (b) number of sessions completed, and (c) an open-ended question asking the reasons for not completing the intervention; (2) *engagement*: (a) percentage of participants who completed homework assignments and frequency of skills practice between sessions and (b) participants’ average number of VR-ACT device log-ins; (3) *retention/attrition*: number of participants who completed the postintervention assessment; (4) *acceptability*: participants will use a Likert-like scale (eg, 0=not at all; 4=very useful) to rate the VR-ACT modules in terms of its *usefulness*, *comprehensibility*, and *likelihood to continue using learned skills*. Participants will provide suggestions to improve the content of sessions via open-ended questions (see Section A in Multimedia Appendix 1).

### Instruments

#### Demographic and Clinical Data

*** ***Demographic data will be collected through a self-report questionnaire (ie, age, marital status, education, sex assigned at birth, gender identity), as well as clinically relevant data (ie, date of stroke, date of pain onset after stroke, poststroke pain diagnosis, current medication, and other chronic pain diagnoses).

#### Primary Outcomes

##### Pain Intensity (Numeric Rating Scale)

The Numerical Pain Rating Scale [37,38] is an 11-point scale used to measure pain intensity, ranging from 0 (“No pain”) to 10 (“Worst imaginable pain”). It assesses pain through 3 ratings: current pain, highest pain in the last 24 hours, and lowest pain in the last 24 hours, which are then averaged to provide a single score of pain intensity.

##### Pain Impact (Pain Disability Index)

 The pain disability index [39] is an 11-point scale (0=“no disability”; 10=“worst disability”), a widely used scale that measures pain disability in 7 daily life domains. Higher scores indicate higher pain disability.

##### Psychological Distress (Depression, Anxiety, and Stress Scale)

 The Depression, Anxiety, and Stress Scale (DASS-21) [39,40] is a 21-item questionnaire composed of 3 subscales designed to measure the negative emotional states of depression, anxiety, and stress. Each of the 3 DASS subscales comprises seven items, which respondents rate on a 4-point severity/frequency scale (0 to 3) in relation to the extent to which they experienced each state over the past week.

